#### Sample size calculation

Based on a sample size calculation 81 school and 3,240 pupils need to be included in the study. This calculation is based on the assumptions that 15% of the intervention condition and 8% of the intervention + prompt condition have ever smoked 24 months after baseline, whereas among the control condition the national prevalence rate of ever smoking is expected to be 24% at the age of 13. We used the OD (Optimal Design) method of Raudenbush [37] with a two-sided significance level of 0.05, a target power of 0.80 and an ICC of 0.04 (based on the study of Ausems et al. [38]) to calculate the sample size.

To calculate the sample size for the utilisation of the website 300 children per condition will be needed (600 children in total). It is assumed that pupils in the intervention + prompt condition will revisit the ‘Fun without Smokes’ website more often, with a mean usage of 5.5 (SD = 0.8). In contrast, children in the intervention only condition will visit the website at least three times (baseline, 12 months and 24 months) and a mean usage of 3.5 is expected.

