## Background

Smoking among children and young adolescents remains a public health problem, causing illness or chronic diseases such as cancer and cardiovascular diseases in older ages [1-3]. Recent national prevalence rates showed that 12% of 12 year old children tried to smoke a cigarette. At the age of 13, this percentage has doubled [4]. Smoking among this age group is a well recognised predictor of later regular smoking, since addiction can occur among 60-90% of those who have smoked only a few cigarettes [5,6]. The earlier people start smoking, the higher their chances of becoming a regular smoker and the more difficult it becomes to quit [7].

Many authors state that smoking prevention programmes should aim at preventing or delaying the start of tobacco use [8], implying the need to target children between the ages of 10 and 12 years [9]. Children increasingly start to experiment with smoking in the transition period from primary to secondary school [10]. Prevention programmes should focus on increasing knowledge and positive attitudes towards non-smoking (anti-smoking attitudes), self-efficacy and skills to refuse cigarettes among children who have never smoked and preventing those who are already experimenting from continuing to smoke [11,12].

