**Figure 1 F1:**
[figure not shown]
Design of ‘Fun without Smokes’.

All participants will be invited to complete the full assessment questionnaire again 12 and 24 months after the baseline questionnaire is completed, to receive repeated feedback letters about changes in smoking status or key determinants (e.g. attitude, social influences and self-efficacy expectations). However, the tailored advice will take into account the answers of the pupils of the previous measurements.

To increase the probability that the intervention will be attractive, 87 pupils from grade 7 and 8 (10-12 year olds) were involved in the development process. Group interviews were performed to select the name, colour scheme and design for the intervention and website. After developing several lay-outs, websites and logos these were presented to children and they were asked to choose their favourite name. ‘Fun without Smokes’ came out as the most popular. Additionally, short animations were developed to make completion of the questionnaire more attractive. In those animations the consequences of smoking were depicted by animals. Children appreciated these animations.

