**Figure 3 F3:**
[figure not shown]
Recruitment of primary schools.

The criteria for inclusion are that primary schools want their final two grades (pupils aged 10-12 years) to participate in the study and the children have computers with Internet access at school and at home. Special education schools and schools using the prevention programme ‘I don’t smoke (either)’ [‘ik (r)ook niet’] were excluded. Schools that were interested in participation received an invitation letter and information brochure via the RHAs or UM. Furthermore, the programme was explained via telephone to the school principal. After two weeks, they were re-contacted by a member of the research team to discuss participation in the effectiveness study. When schools were interested in participation, agreement with inclusion criteria was checked.

Parents and children were informed about the procedure and goals of the study by means of a letter that children could take home for their parents. All students in grade seven of a participating school were included in the study unless they or their parents refused to be involved. By signing the informed consent letter and returning this to the research team, parents and children were able to deny participation before the start of the study. Additionally, they were able to withdraw participation at any moment by e-mail, telephone or in person during the entire study period.

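### The 24% control rate is the national figure for age 13, but grade-7 pupils will be about 12 to 13 at 24 months, so 24% is the upper end of the protocol's own range

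*Protocol article*

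**What the plan says.** In the Protocol article, Sample size calculation, the 24-month rates are fixed as follows: "15% of the intervention condition and 8% of the intervention + prompt condition have ever smoked 24 months after baseline", and "among the control condition the national prevalence rate of ever smoking is expected to be 24% at the age of 13". The other inputs are a two-sided level of 0.05, power 0.80 and ICC 0.04, giving 81 schools and 3,240 pupils.

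The Background gives the national series behind the control rate: "12% of 12 year old children tried to smoke a cigarette. At the age of 13, this percentage has doubled".

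On who is enrolled, Recruitment procedure says: "All students in grade seven of a participating school were included in the study unless they or their parents refused to be involved". The same section, and Intervention framework and procedures, give 10 to 12 years for grades 7 and 8 together. Under Procedure, the 12-month assessment follows the baseline in-school routine, and the 24-month questionnaire is completed at home because pupils have by then left primary school. Strengths and limitations expects about 60% drop-out at the final measurement and says that the sample size allows for it.

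**The concern.** On the protocol's figures the ever-smoking rate rises by 12 percentage points between ages 12 and 13. The expected age at the 24-month assessment therefore largely determines the control rate. Grade 7 is the lower of two grades spanning 10 to 12 years, so its pupils should be about 10 to 11 at baseline and 12 to 13 two years later. Using the age-13 rate for all of them takes the upper end of the range.

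What is at stake is the power to compare control with the intervention without prompts, which is part of the first hypothesis. If fewer control pupils have ever smoked, a given proportional reduction is a smaller absolute difference and is harder to detect.

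**Working it through.** **Inputs**
- Arm rates of 24%, 15% and 8%, ICC 0.04, two-sided 0.05, 81 schools and 3,240 pupils: Sample size calculation.
- 12% at age 12 and 2 × 12% = 24% at age 13: Background.
- 60% drop-out: Strengths and limitations.
- Assumed: equal allocation (81/3 = 27 schools per arm), 3,240/81 = 40 pupils per school, and even drop-out, so 0.4 × 40 = 16 retained per school.
- Assumed: the share w of pupils aged 13 at 24 months, which is not stated.

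**Effective size per arm.** The design effect is 1 + (16 − 1) × 0.04 = 1.60. Effective n = 27 × 16 / 1.60 = 270.

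**The plan's own figure.** For 24% versus 15% at 80% power with pooled variance, n = (1.96 × 0.5603 + 0.8416 × 0.5567)² / 0.09² = 303.03, or 304 per arm. With 60% drop-out this needs 304 × 1.60 / 16 = 30.4, so 31 schools per arm, or 93 in all. With no drop-out (40 per school, design effect 2.56) it needs 19.5 per arm. The stated 27 per arm matches neither.

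**Power formula.** Power = Φ{[Δ√n − 1.96√(2p̄(1−p̄))] / √(p₁(1−p₁) + p₂(1−p₂))}, with n = 270.
- 24% versus 15%: (0.09 × 16.43 − 1.96 × 0.5603) / 0.5567 = 0.68, so power is 75%. This is the baseline before any question of age.
- 18% versus 11.25%: (0.0675 × 16.43 − 1.96 × 0.4997) / 0.4974 = 0.26, so power is 60%.

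**Control rate by age mix.** Control rate = 0.24w + 0.12(1 − w). The relative column keeps the planned ratio 15/24 = 0.625. The absolute column keeps 9 points.

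| Share aged 13 (assumed) | Control rate | Intervention rate, relative | Power, relative | Power, absolute |
|---|---|---|---|---|
| 100% | 24% | 15% | 75% | 75% |
| 75% | 21% | 13.1% | 68% | 81% |
| 50% | 18% | 11.25% | 60% | 87% |
| 25% | 15% | 9.4% | 52% | 93% |

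At a control rate of 18% with the ratio kept, n is 430 per arm, or 430 × 1.60 / 16 = 43 schools per arm and 129 in all.

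**Other contrasts**
- Control versus intervention + prompt, with its ratio 8/24 kept: above 99% at 24% versus 8%, 99% at 18% versus 6%, and 97% at 15% versus 5%.
- Intervention versus intervention + prompt: 15% versus 8% does not use the control rate, and its power is 72% under the same drop-out. It falls (to 58% at 11.25% versus 6%) only if both active-arm rates are scaled down too.

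**The case against.** The case on the other side has several parts.

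- **The age is inferred.** The protocol gives no age for grade 7 alone and none for the 24-month assessment. A pupil aged 11 at baseline is 13 at 24 months, exactly the age used. The Abstract describes the target group as 10 to 13, so some pupils could be older than 13 at follow-up. This stands: the size of the overstatement cannot be fixed from the document. It does not justify treating the whole cohort as 13.
- **The loss of power depends on the effect model.** The plan states arm rates, not a relative reduction, and with the 9-point difference kept power rises. This stands, so a reader should not infer that a lower control rate reduces power in every case. But 9 points from 18% is a halving, against a planned reduction of 9/24 = 37.5%, and the Background describes the effects of earlier in-school programmes as small.
- **The gap to 80% is not all due to age.** This stands. The step from 80% to 75% comes from applying 60% drop-out to 81 schools. Age accounts only for what lies below 75%.
- **There may be room.** Recruitment procedure reports 175 schools willing to take part, more than the 129 above. Willing schools are not yet enrolled schools, and the stated requirement remains 81.

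Two stronger readings are tempting. One sets an 18% control rate against the stated 15% and finds 15% power. That lowers the control arm for age but not the intervention arm, although pupils in both would be equally young. The other sees a contradiction between the inclusion criterion of the final two grades and the enrolment of grade seven. Read with Procedure, this is most simply one cohort starting in grade 7 and passing through both grades.

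**Conclusion.** The point holds in a limited form. The control rate of 24% is the upper end of what the protocol's own figures imply for a cohort of about 12 to 13 years, and no reason is given for using it for everyone. With the planned relative reduction kept, power for control versus intervention falls from 75% to 68%, 60% or 52% at control rates of 21%, 18% or 15%.

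These figures rest on equal arms, 16 retained pupils in each of 27 schools per arm, and an assumed age split. Control versus intervention + prompt stays at about 97% or more over the same range if its relative reduction is kept. The contrast between the two active arms is touched only if their rates are restated as well. The documents do not support a claim that all the primary comparisons are underpowered because of age, or any single figure for the loss.

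**What to change.** In Sample size calculation:
1. State the expected ages at the 24-month assessment, and replace 24% with the age-weighted rate from the protocol's 12% and 24%.
2. Say whether the intervention effect is assumed relative or absolute, and restate the arm rates to match.
3. Restate the power for control versus intervention over control rates of about 15% to 24%, after the 60% drop-out, showing the 24% case so that the effect of age is separate from that of drop-out.

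The cost is a revised planning paragraph and, under a relative effect, a less favourable stated power. Enrolment does not change.

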### Evaluation design

#### Objectives and design

Both versions of the ‘Fun without Smokes’ programme (intervention and intervention + prompt condition) will be evaluated in a cluster randomised controlled trial with a no information control condition. The aim is to test the effectiveness of the programme on prevention of smoking initiation and on cognitions in favour of non-smoking at 12 and 24 months post baseline, as well as the additional effect of prompts on the usage of the website and on the outcome measures. Schools were the units of randomisation.

Assessment of smoking behaviour and smoking related cognitions will be at baseline and 12 and 24 months later, by means of web-based questionnaires.

Ever smoking is chosen as the primary outcome measure, because prevalence rates of monthly smoking are generally low at the age of 13 (8% at this age in 2010 [4]). Additionally, the level of utilisation of the website will be a primary outcome measure. This outcome will be operationalized as the number of visits to the ‘Fun without Smokes’ website and is expected to be significantly higher in the intervention + prompt condition compared with the intervention condition. Secondary outcome measures are attitudes, social influences, self-efficacy, intention to smoke and monthly smoking.

The hypotheses for this study are:

1. Providing children with computer-tailored feedback about non-smoking will prevent smoking initiation;

2. Children receiving computer-tailored feedback about non-smoking will have stronger cognitions in favour of non-smoking;

3. Computer-tailored feedback about non-smoking and prompting children through e-mail and SMS to revisit the website will result in a stronger effect on the prevention of smoking initiation (and on cognitions in favour of non-smoking) than tailored feedback only;

4. Children receiving computer-tailored feedback, SMS and e-mails will visit the website more often than children receiving computer-tailored feedback only.

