### Strengths and limitations

Previous in-school smoking prevention programmes required much investment in time from the participating (primary) schools [45], leading to frustration and higher drop-out rates of participants or schools. The ‘Fun without Smokes’ programme is a web-based intervention, which requires only a very limited input and time from teachers, and thus meets the needs of schools to lower workloads involved in implementing smoking prevention programmes. A second strength is the design of the effectiveness study, since it assesses effects not only immediately, but also after 12 and 24 months. This allows testing both the short- and long-term effects of the ‘Fun without Smokes’ programme.

A possible limitation of the study is that smoking behaviour and other factors related to smoking are based on self-reports of youngsters, which might lead to measurement errors (i.e. social desirable answers). To avoid social desirable answers, we will guarantee full confidentiality to our participants. The validity of adolescent self-reported smoking has been shown to be high in accordance with biological indicators when measurement assures confidentiality [46]. Approximately 60% is expected to drop-out in the final measurement, since pupils are not connected to their primary school anymore. This drop-out percentage is taken into account in the sample size calculation. The large sample size will guarantee enough power for the evaluation study.

If the programme is proven to be effective, it will be a valuable tool for smoking prevention that can readily be implemented in primary schools in the Netherlands. This study will, furthermore, provide valuable information about the usability and additional effects of SMS and e-mail reminders in combination with a computer-tailored feedback programme.

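### The 300 pupils per condition for website utilisation do not follow from the stated means and SD, and the assumed minimum of three visits conflicts with the expected 60% drop-out

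*Protocol article*

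**What the plan says.** Under Objectives and design, the protocol article makes use of the website a primary outcome alongside ever smoking: "This outcome will be operationalized as the number of visits to the" programme's website. More visits are expected with prompts than without.

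Under Sample size calculation, the article gives this outcome its own size: "To calculate the sample size for the utilisation of the website 300 children per condition will be needed (600 children in total"). It also gives the inputs behind it. The prompt arm is expected to revisit more often, "with a mean usage of 5.5 (SD = 0.8"). For the arm without prompts, "a mean usage of 3.5 is expected", and pupils there "will visit the website at least three times (baseline, 12 months and 24 months"). No significance level, power, ICC or drop-out is given for this calculation. The smoking calculation in the same section uses a two-sided 0.05, power 0.80 and an ICC of 0.04, and arrives at 81 schools and 3,240 pupils.

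Under Procedure, the baseline and 12-month questionnaires are completed in class under a teacher, and the 24-month questionnaire at home by invitation. Under Strengths and limitations, "Approximately 60% is expected to drop-out in the final measurement".

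**The concern.** The article prints both the inputs and the result, so the calculation can be checked from the text. A difference of 2 visits with an SD of 0.8 is a standardised difference of 2.5, which is very large. A requirement of 300 per arm belongs to a standardised difference of about 0.23. One of the printed figures must be wrong, or an input that matters is unstated. Until that is settled, a reader cannot tell what difference in use the trial was sized to detect.

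The visit assumption raises a second problem. The three visits taken as a minimum fall at the three questionnaire time points, yet the article expects most pupils to be lost at the last of them.

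**Working it through.** **Inputs.** From Sample size calculation: means 5.5 and 3.5 (difference 2.0), SD 0.8, 300 per condition, and 3,240/81 = 40 pupils per school. From Strengths and limitations: 60% drop-out at the final measurement. Assumed: two-sided 0.05, power 0.80 and ICC 0.04 carry over from the smoking calculation, and SD 0.8, given for the prompt arm only, holds in both arms.

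**Attempt to reproduce 300.**

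- Unclustered, normal approximation: n = 2(1.96 + 0.8416)² × 0.8²/2.0² = 2.51, so 3 per arm.
- Unclustered, t-test: n = 3.76, so 4 per arm (power 0.64 with 3 and 0.84 with 4).
- Design effect: 1 + (40 − 1) × 0.04 = 2.56.
- With clustering: 2.51 × 2.56 = 6.4, so 7 per arm. Starting from 4, 4 × 2.56 = 10.24, so 11 per arm.
- With 60% drop-out as well: 10.24/0.4 = 25.6, so 26 per arm.

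**Do other choices close the gap?**

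- Power of 0.999 needs 9-10 per arm unclustered. A one-sided test at 80% power needs 2-3.
- Starting from 4 per arm with 40 per school and 60% drop-out, an ICC of 0.5 gives 205 and an ICC of 1 gives 400. Only an implausible ICC between these would give 300.
- A Poisson variance equal to the mean of 5.5 (SD about 2.3) in both arms gives 2 × 2.8016² × 5.5/2.0² = 21.6. That is 55.3 after × 2.56 and 138.1 after /0.4, so 139 per arm, still under half of 300.

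**Reading 300 backwards, without clustering.**

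- Detectable standardised difference: 2.8016 × √(2/300) = 0.229.
- At SD 0.8 this is 0.229 × 0.8 = 0.18 visits.
- For a difference of 2.0 visits, the SD would have to be 2.0/0.2287 = 8.7.
- With design effect 2.56 (300/2.56 = 117 effective pupils), the corresponding figures are 0.29 visits, or an SD of 5.5.

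Power for the stated effect with 300 per arm is essentially 1.00.

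**The minimum of three visits.** If every pupil completes baseline and 12 months and 40% complete 24 months, scheduled visits average 1 + 1 + 0.4 = 2.4. This is an upper limit, because it allows for no loss at 12 months. About 60% of pupils would have at most two scheduled visits, so three is not a minimum. A mean of 3.5 then needs 3.5 − 2.4 = 1.1 other visits per pupil, against the 3.5 − 3 = 0.5 that the text implies.

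**What the planned sample can detect.** There are 3,240/3 = 1,080 pupils per arm. With design effect 2.56, the detectable difference is 2.8016 × √(2 × 2.56/1,080) = 0.193 SD. That is 0.15 visits at SD 0.8 and 1.7 visits at SD 8.7, if web-logs are counted for all planned pupils.

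**The case against.** The strongest defence is that nothing turns on the error. Recruitment is set by the smoking outcome, at about 1,080 pupils per arm, or 1,080 × 0.4 = 432 if 60% are lost. Both exceed 300, and 300 far exceeds what the stated inputs require. Web-logs also do not depend on a pupil returning the questionnaire. This stands, and it limits the point to an untraceable calculation. A reader might infer that the utilisation comparison is underpowered, but the stated inputs do not show that.

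It is also fair to say that significance level, power and ICC are stated only for smoking, and the SD for one arm only. The comparison figures above therefore rest on assumptions. No usual choice brings the result near 300, however. A fuller protocol might hold further inputs, but the article prints a size next to inputs that do not support it.

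On the visits, 60% drop-out contradicts three as a minimum but does not rule out a mean of 3.5, because pupils may visit as often as they like between measurements.

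A reader might go further and say that the scheduled sessions are compulsory and are not real use of the programme. The article does not support this. Completing the questionnaire generates the feedback letters, intervention pupils see feedback summaries on screen after the baseline and 12-month questionnaires, and questionnaire completion is listed among the logged website components. The 24-month session is by invitation at home, and families may refuse or withdraw.

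Nor does it help to subtract three visits from each mean and say that the arm ratio rises from 5.5/3.5 = 1.6 to 2.5/0.5 = 5.0. That uses three visits per pupil where at most 2.4 are expected; with 2.4 the ratio is 3.1/1.1 = 2.8. The article announces no ratio analysis, and equal scheduled visits in both arms leave the difference of 2.0 unchanged.

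**Conclusion.** The point holds as an error in a stated sample size for a primary outcome. The inputs give 3-4 pupils per arm unclustered, about 7-11 with clustering and about 26 with drop-out as well, so 300 is more than ten times the most generous of these. Either the SD, the means or the 300 is misstated, and the article does not show which. The result assumes that the smoking calculation's error rate, power and ICC carry over and that SD 0.8 is common to both arms.

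Separately, three visits as a minimum for the arm without prompts cannot stand beside 60% drop-out at the final measurement. Both matters call for correction of the text. Neither shows that the trial is too small or that counting visits is an invalid outcome.

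**What to change.** Restate the utilisation calculation so that a reader can reproduce it:

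- give the significance level, power and ICC used, and an SD for each arm suited to a count of visits;
- include the school design effect;
- replace the minimum of three visits with assumptions that fit the 60% drop-out;
- state the difference that the planned pupils, about 1,080 per arm, can detect.

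This changes text only. No more pupils are needed on the stated inputs. Even at an SD of 8.7, the planned number would detect about 1.7 visits under the ICC assumed here.

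As an optional, inexpensive addition, report visits other than the three scheduled questionnaire sessions as a supporting analysis. The scheduled sessions occur in both arms and are not prompted revisits, so this count bears more directly on what the prompts add. Under Utilisation of the website, the logs already record user, date and component, so no new data are required. The cost is a little more analysis work, and the primary outcome can stay as it is.
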